### Criteria for discontinuing or modifying allocated interventions {11b}

All surgeons conducting liver resections in this study are senior surgeons with years of experience in hepatobiliary surgery. If a case is particularly demanding and the surgeon asks for another demonstration mode, this wish will be granted. During operation, the conventional 2D CT scans will be available to the surgeon, as well as the 3D print and the 3D PDF for the respecting groups. Due to technical restrictions, 3D VR using a head-mounted display will not be used in the operating room.

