### Intervention description {11a}

After written consent, the patients are randomized into one of four groups using an envelope system. Randomization is not conducted by the researchers but by an impartial study nurse. Reconstruction of the preoperative CT scan into a 3D data set is performed by the researchers of the study group in the program Synapse 3D (Fujifilm Europe GmbH, Düsseldorf). In case of randomization into the 3D print group, the data set is anonymized and STL files are sent to a cooperating company (Cella Medical Solutions, Murcia, Spain) for printing. According to randomization, the 3D data set is then displayed to the surgeon assigned to the case not later than the day before surgery for resection planning. The surgeon is assisted by a member of the study group in terms of technical support and calculation of the planned resection volume (RLV1). At the end of surgery, the actual resection volume (RLV2) is determined by water displacement volumetry. A questionnaire about usability and subjective task load using the System Usability Scale (SUS) [19] and NASA Task Load Index (TLX) [20] is presented to the surgeons after operation. The data will be collected in a local database, to which only researchers of the study group have access. Data will be stored for 10 years according to the requirements of the local ethics committee.

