### Outcomes {12}

Primary outcome is the quotient of planned resection volume (RLV1) and actual resection volume (RLV2) calculated as (RLV2-RLV1)/RLV1. The resection volume will be measured in millilitres; planned resection volume will be measured using one of the four demonstration modes and volumetry no late than the day before surgery. Actual resection volume will be measured the day of surgery. This parameter is critical to determine how accurate the predicted resection volume is between the different groups.

Secondary outcome consists of usability and subjective task load using SUS and the NASA TLX. A system is less likely to be used, if it is complicated or the controls are hard to remember or challenging to conduct. Thus these scores will show if implementation into daily clinical use is feasible for the different demonstration modes. The described systems are being tested in order to simplify liver resection planning and teaching, thus these measures are critical to determine usability and likelihood of daily use.

Furthermore, patients’ characteristics as well as intraoperative outcome (i.e. resection margin, blood loss, duration of surgery), pathological findings and postoperative morbidity and mortality are assessed in order to describe the study collective properly. Since liver resections can vary greatly in extent even in the chosen group of major resections, it is important to put patients’ characteristics and intraoperative and postoperative measures into perspective with the planned and actual surgical procedure.

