### Plans to promote participant retention and complete follow-up {18b}

Since there is only a short follow-up period and no special action by the patients needed, there is no specific plan to facilitate the completion of follow-up. Data of patients who withdraw consent for the study, will not be used in analyses. If the surgeon in charge decides to take the patient out of their randomized group (i.e. in especially demanding cases) data will still be collected for an “as intended” analysis and in order to analyse all patients, who have been taken out of their randomized group.

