## Statistical methods

### Statistical methods for primary and secondary outcomes {20a}

The primary analyses of the trial will adopt the per-protocol set (PPS), since there are only few dropouts to be expected. Patients withdrawing consent will not be included in analyses. Patients dropping out, due to a senior surgeons’ decision, will be analysed following the intention-to-treat (ITT) principle. The primary outcome, which is the quotient (RLV2-RLV1)/RLV1, will be analysed using the Wilcoxon Test. Continuous variables, as in the patients’ characteristics and perioperative and postoperative outcome, will be presented as mean ± standard deviation or median including interquartile range, depending on distribution. In order to compare the different study groups, an independent t-test will be applied. Variables with dichotomous values will be analysed using chi-square test.

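### After a switch of demonstration mode, the protocol neither secures a planned volume (RLV1) from the allocated mode nor says which RLV1 enters the primary endpoint

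*Protocol article*

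**What the plan says.** All references are to the protocol article.

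- **Outcome** (Outcomes {12}): "Primary outcome is the quotient of planned resection volume (RLV1) and actual resection volume (RLV2) calculated as (RLV2-RLV1)/RLV1". RLV2 is measured on the day of surgery. Explanation for the choice of comparators {6b} gives the aim as finding the mode that predicts resection volume most accurately.
- **Source of RLV1** (Outcomes {12}): "planned resection volume will be measured using one of the four demonstration modes and volumetry no late than the day before surgery".
- **Display** (Intervention description {11a}): "According to randomization, the 3D data set is then displayed to the surgeon assigned to the case not later than the day before surgery". A study member helps the surgeon to calculate RLV1.
- **Switching** (Criteria for discontinuing or modifying allocated interventions {11b}): "If a case is particularly demanding and the surgeon asks for another demonstration mode, this wish will be granted". No arm, direction or time point is specified.
- **Data on switched patients** (Plans to promote participant retention and complete follow-up {18b}): the case is introduced with "If the surgeon in charge decides to take the patient out of their randomized group". Data collection goes on, both for an analysis by intended group and for an analysis of the moved patients.
- **Analysis sets** (Statistical methods for primary and secondary outcomes {20a}): the per-protocol set is primary, but "Patients dropping out, due to a senior surgeons’ decision, will be analysed following the intention-to-treat (ITT) principle".

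**The concern.** Keeping switched patients in their randomised arm is ordinary intention-to-treat practice, and some dilution comes with it. This trial differs in one respect: the mode that the surgeon switches to can itself generate part of the endpoint. If planning moves to another mode and only the final plan is recorded, the patient's RLV1 is that other mode's prediction.

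The allocated mode's own prediction, which the trial sets out to compare, is then lost. It cannot be recovered after surgery without hindsight, so a later analysis plan cannot repair the gap. Switching is tied to demanding cases, so the affected patients are not a random sample.

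**Working it through.** **1. What happens to RLV1 when a surgeon switches**

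| Question | What the protocol fixes |
|---|---|
| Which mode is shown for planning? | The allocated one ({11a}) |
| May another mode be used? | Yes, on request in a demanding case ({11b}) |
| Must RLV1 be recorded before the switch? | Not stated |
| Which RLV1 counts if there are two? | Not stated; {12} refers to one of the four modes |
| Where is the patient analysed? | Primary set is per-protocol; surgeon-decision cases follow intention-to-treat ({20a}) |

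Under intention-to-treat the patient keeps the allocated label, but RLV1 may come from another mode. Under a per-protocol rule that removes switched patients, the arm loses demanding cases. Neither route guarantees that the allocated mode's prediction is available.

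**2. The plan's own sample-size figure**

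Sample size {14} gives a two-sided t test, local level 0.017, power 80%, SD 20% (control) and 10% (each 3D group), and 23 per group raised to 25. It states no mean difference, so 23 cannot be reproduced forwards. Solving backwards:

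- Root-mean-square SD = √((20² + 10²)/2) = 15.81.
- 23 per group at 0.017 and 80% power needs a standardised effect of 0.984.
- 0.984 × 15.81 ≈ 15.6 percentage points.

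**3. Illustration on absolute error**

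Assumptions, not document figures: errors are normal and centred at zero in both arms, with the {14} SDs. Exactly k of 25 controls have an RLV1 from a 3D mode and then have SD 10%. Accuracy is read as absolute error.

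Mean absolute error = SD × √(2/π) = SD × 0.798, that is 16.0% in control and 8.0% in a 3D arm, a contrast of 8.0 points. With k switched controls the contrast is 7.98 × (1 − k/25). Power is simulated, two-sided at 0.017, 25 per arm.

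| k of 25 | Control mean absolute error | Contrast (points) | Wilcoxon power | Welch power |
|---|---|---|---|---|
| 0 | 16.0% | 8.0 | 55% | 70% |
| 2 | 15.3% | 7.3 | 46% | 61% |
| 5 | 14.4% | 6.4 | 33% | 48% |
| 7 | 13.7% | 5.7 | 26% | 38% |

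Removing five controls at random instead gives Welch power of about 57%, before allowing for the fact that the removed cases would be the demanding ones.

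**4. The same inputs on the printed, signed outcome**

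With both arms centred at zero, the signed quotient has power of about 2% at every k, so switching changes nothing measurable. Switching matters on the signed scale only if the modes differ in mean error. With the back-solved 15.6 points and switched controls behaving like 3D patients, the expected difference is 15.56 × (1 − f) for a switched share f. At f = 8% that is 14.3 points and at f = 20% it is 12.4. The t-test power at 25 per arm goes from 84% to 77% and 65%.

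**5. What keeping the allocated-mode RLV1 can do**

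If the second mode changes the resection, RLV2 belongs to the revised plan. Suppose the plan change adds an independent error of SD 10% or 20% in 5 switched controls:

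- SD 10%: √(20² + 10²) = 22.4, times 0.798 = 17.8. Control mean = (20 × 15.96 + 5 × 17.84)/25 = 16.3%.
- SD 20%: √(20² + 20²) = 28.3, times 0.798 = 22.6. Control mean = (20 × 15.96 + 5 × 22.57)/25 = 17.3%.

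Welch power rises from 70% to 73% or 78%. The allocated-mode value can therefore err in the opposite direction, in favour of 3D when the switched patients are controls.

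**The case against.** The strongest objection is to the remedy. Setting an allocated-mode RLV1 against the RLV2 of a revised plan mixes prediction error with plan change, and step 5 shows that this can inflate the allocated arm's error. This stands. For that reason the allocated-mode value should not be presented as free of bias, and the analysis should be repeated with the final-plan RLV1.

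Second, the sentence on the source of RLV1 in {12} reads most naturally as one mode per group, and {11a} displays the data set by allocation. This also stands. A reader might infer that the protocol lets RLV1 come from any mode at will; it does not say so. The gap is confined to patients whose surgeon switches.

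Third, a reader might infer that an intention-to-treat analysis would systematically credit the control arm with 3D predictions, or that the trial's primary analysis falls from 70% to 38% power. The documents support neither:

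- They give no rate or direction of switching. A switch could be between two 3D modes or from 3D to CT, and RLV1 might in practice already have been recorded when the request is made.
- The 70% to 38% figures rest on absolute errors and a Welch test, whereas the plan states a signed quotient, a Wilcoxon test and a primary per-protocol set.
- The model gives switched cases the average 3D spread, although they would be demanding ones. Since {11b} limits switching to particularly demanding cases and {20a} expects few dropouts, 5 or 7 of 25 is at the high end.

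Finally, dilution under intention-to-treat is normal, and {18b} already plans to look at the moved patients separately. That is true, but neither analysis can use an RLV1 that was never recorded.

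**Conclusion.** The point holds as a gap in how the primary endpoint is defined and recorded for switched patients. The protocol allows the switch and keeps the patients' data, but it neither secures the allocated mode's RLV1 nor says which RLV1 is analysed. The provisions in {18b} and {20a} also leave open whether these patients reach the primary result through the intention-to-treat sentence or are removed by the per-protocol set, and they need to be reconciled.

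The size of the effect cannot be derived from the documents. If switched controls take on the 3D arm's error distribution, the contrast shrinks in proportion to the share switched: by 8% with 2 of 25 and by 20% with 5 of 25. The absolute-error Wilcoxon figures of about 55%, 46% and 33% show what that could mean under the stated assumptions. They are not the power of the planned signed per-protocol analysis.

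This is a worthwhile, inexpensive improvement and not a flaw that invalidates the trial. It has to be made prospectively. Whether switching should be allowed is a clinical matter and is not judged here.

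**What to change.** - In {11a}, {11b} and {12}, state that RLV1 is calculated with the allocated mode and dated on the CRF before another mode is shown. Access to other modes otherwise stays as it is.
- After a switch, also record the mode used and a second RLV1 from the final plan.
- In {20a}, use the allocated-mode RLV1 in the intention-to-treat analysis and repeat that analysis with the final-plan RLV1 as a sensitivity analysis. Report the number and direction of switches by arm. Reconcile the per-protocol and intention-to-treat sentences with {18b}.

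The cost is a sentence in each section, a small CRF addition and a few minutes of planning in switched cases, because the first calculation has to be finished before the second mode is opened. The remaining weakness is that a changed resection makes the allocated-mode error include the plan change. The final-plan analysis credits the switched-to mode instead, so the two results together show the range.

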### Strategies to improve adherence to interventions {11c}

Adherence to intervention will be boosted by the technical support by the research group. Especially for surgeons, who have not used a VR head-mounted display before, help and guidance are necessary in the beginning. It is to be expected that the support needed will decrease during the course of the study.

### Relevant concomitant care permitted or prohibited during the trial {11d}

Not applicable to this trial. There are no restrictions regarding concomitant care during the trial. Using 3D PDF, 3D print or 3D VR in addition to regular cross-section imaging will not require alteration to usual care pathways for liver resection (including medication, drainages, sutures or imaging after surgery).

### Provisions for post-trial care {30}

There is no specific post-trial care. The patients are treated in the hospital for the time needed for them to recover. Most patients visit the out-patient clinic about two weeks after discharge for a regular check-up and about three months after surgery for regular tumour aftercare. The patients included in the study do not differ in this regard from other patients, so no special care is needed. There is no compensation for patients of any kind and there is no harm or higher risk of complication to be expected, since the method of operation is not altered.

### Outcomes {12}

Primary outcome is the quotient of planned resection volume (RLV1) and actual resection volume (RLV2) calculated as (RLV2-RLV1)/RLV1. The resection volume will be measured in millilitres; planned resection volume will be measured using one of the four demonstration modes and volumetry no late than the day before surgery. Actual resection volume will be measured the day of surgery. This parameter is critical to determine how accurate the predicted resection volume is between the different groups.

Secondary outcome consists of usability and subjective task load using SUS and the NASA TLX. A system is less likely to be used, if it is complicated or the controls are hard to remember or challenging to conduct. Thus these scores will show if implementation into daily clinical use is feasible for the different demonstration modes. The described systems are being tested in order to simplify liver resection planning and teaching, thus these measures are critical to determine usability and likelihood of daily use.

Furthermore, patients’ characteristics as well as intraoperative outcome (i.e. resection margin, blood loss, duration of surgery), pathological findings and postoperative morbidity and mortality are assessed in order to describe the study collective properly. Since liver resections can vary greatly in extent even in the chosen group of major resections, it is important to put patients’ characteristics and intraoperative and postoperative measures into perspective with the planned and actual surgical procedure.

### Participant timeline {13}

The participant timeline is shown in Table 1.

**Table 1 Tab1:** Participant timeline

	Study period					
	Enrolment	Allocation	Post-allocation			
Timepoint	***− 1 day−0***	0	***+2 week***	***Day of surgery***	***POD 30***	***POD 90***
**Enrolment:**						
**Eligibility screen**	X					
**Informed consent**	X					
**Allocation**		X				
**Interventions:**						
***3D PDF***			X			
***3D print***			X			
***3D VR***			X			
***Control***						
**Assessments:**						
***Patients’ characterisctis***	X					
***Planned resection volume***			X			
***Preoperative questionnaire (planned resection)***			X			
***Postoperative questionnaire (SUS, NASA TLX, teaching experience)***				X		
***Actual resection volume***				X		
***Intraoperative specifics***				X		
***Pathological findings***					X	
***30-day morbidity (Dindo-Clavien)***					X	
***30-day mortality***					X	
***90-day mortality***						X

### Sample size {14}

Sample size was calculated in collaboration with the Institute of Medical Biostatistics, Epidemiology and Informatics (IMBEI) and the Interdisciplinary Center for Clinical Trials (IZKS), University Medical Center of the Johannes Gutenberg-University Mainz using G*Power (Düsseldorf, Germany) and a two-sided *t* test [21]. A power of 80% with a global significance level of 5% and a local significance level of 0.017 was chosen. Assuming a standard deviation of the mean of 20% in the control group and 10% in each 3D group, a number of 23 patients per group was calculated. Because of possible dropouts, we decided to increase the case number to 25 per group, deeming the total trial population *n* = 100.

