
A previously conducted preclinical study compared the three modalities and found an improved visualization in 3D VR with head-mounted displays and 3D print [16]. In the current study, the clinical application of the described systems in a prospective randomized controlled trial is the focal point.

The interventions are compared to the current standard of viewing the CT scan on a regular computer screen. Therefore there is no placebo or sham group in action, which could potentially harm a patient. The regular CT scans are available to the surgical team at all times, during planning as well as during operation. The interventions act as supplement to the gold standard and have the potential to not only aid the surgeon but also the teaching of residents and students. The trial is expected to show, which demonstration modality of 3D models is helpful for liver resection planning and which demonstration mode facilitates the highest usability and best outcome. Generating a 3D model of the liver is a time-consuming task [7] and costs of 3D prints and VR head-mounted displays and personal computers capable of displaying VR content make economical deliberations necessary and obvious. The results of this study may help in the decision process, whether these techniques should and can be applied on a regular basis or only for well-chosen cases.

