## Interventions

### Explanation for the choice of comparators {6b}

Resection volume in liver surgery is a critical parameter correlating both to liver failure as well as postoperative morbidity. The presented trial aims to compare planned resection volume and actual resection volume throughout the aforementioned demonstrations modes to see which mode enables the most accurate prediction of resection volume. Furthermore, usability scores and handling of the different demonstration modes will be compared to determine, if one mode is preferable over the others. Patients’ characteristics as well as intraoperative outcome and postoperative morbidity and mortality are recorded for descriptive statistics and to unveil any imbalances of the study group. To compare patients’ general condition, the Charleson Comorbidity Index [17] is used; to assess postoperative complications, Dindo-Clavien Score and the comprehensive compication index are used.  (DOI: 10.1097/SLA.0000000000002902 [18]).

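### The local level of 0.017 covers only the three 3D-versus-control comparisons; the 3D-versus-3D comparisons needed to name a most accurate mode have no share of the 5%, and Holm would use that 5% better

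*Protocol article*

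**What the plan says.** The protocol article sizes the trial with "a two-sided *t* test" and adds: "A power of 80% with a global significance level of 5% and a local significance level of 0.017 was chosen". It names neither the multiplicity procedure nor the comparisons that the local level serves. The variability assumption separates the control from the 3D arms: "Assuming a standard deviation of the mean of 20% in the control group and 10% in each 3D group". From this, "a number of 23 patients per group was calculated", and "we decided to increase the case number to 25 per group" to allow for dropout. No difference in means is given.

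Objectives {7} sets the three 3D displays against the conventional CT display. Explanation for the choice of comparators {6b} goes further. It says of the primary outcome that the trial should reveal which mode predicts resection volume most accurately, and it says of usability and handling that they are compared "to determine, if one mode is preferable over the others". Background and rationale {6a} expects the trial to show "which demonstration mode facilitates the highest usability and best outcome".

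Statistical methods {20a} assigns a Wilcoxon test to the primary outcome without naming pairs or a family. Its later sentence, "In order to compare the different study groups, an independent t-test will be applied", follows the text on patient characteristics and perioperative variables and does not settle the matter for the primary outcome. Trial design {8} calls the trial exploratory.

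**The concern.** A protocol that promises a global 5% and fixes a numerical local level should make clear which claims that 5% covers. Four groups give six pairs. A local level of 0.05/3 pays for three of them, but a statement that one 3D mode is more accurate than another rests on the other three.

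Two things are at stake. If the trial tests all six pairs at 0.017, the global 5% no longer holds for the whole set. If it tests only the three control comparisons, a conclusion ranking the 3D modes has no error control behind it, although {6a} expects the results to inform whether these costly techniques are used routinely. A smaller, separate point is that a fixed threshold for all three tests leaves power unused that a step-down procedure would recover at the same 5%.

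**Working it through.** **Inputs from the Sample size section.** Global level 0.05, local level 0.017, power 80%, two-sided t test, 20% in control and 10% in each 3D group, 23 per group raised to 25.

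**What the local level covers.** 0.05/3 = 0.01667, which rounds to 0.017. The rounding excess is trivial: 3 × 0.017 = 0.051. Six pairs by the same rule would need 0.05/6 = 0.0083.

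**The stated 23 per group.** This cannot be reproduced, because no difference in means is given. It can only be back-solved (noncentral t, two-sided 0.017):
- Standardized difference d = 1.0: n = 23 gives power 0.814.
- Reading 20% and 10% as standard deviations: pooled SD = √((20² + 10²)/2) = 15.81, and n = 23 gives power 0.80 at a difference of 15.56 points (15.56/15.81 = 0.98).

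Both are assumptions and are used below only as such.

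**Family-wise error at 0.017 per test.** For six pairs, the Bonferroni bound is 6 × 0.017 = 0.102; if the tests were independent it would be 1 − (1 − 0.017)⁶ = 0.098. The pairs share groups, so the actual rate is lower. Simulation with normal data, t tests and 23 or 25 per group, all four means equal:

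| Set tested at 0.017 | Equal SDs | SDs 20/10/10/10 |
|---|---|---|
| Three 3D v control | 0.045 | 0.038 |
| All six pairs | 0.079-0.080 | 0.078 |
| Three 3D v 3D only | 0.045 | 0.045 |

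Rank-sum tests give the same picture: about 7 to 8% for six pairs and about 4% for the three control comparisons. The last row matters: if control differs and the three 3D modes are equal, testing the 3D pairs at 0.017 gives 4.5%. The excess therefore arises mainly when all four groups are equal.

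**Holm against a fixed 0.05/3 for the three control comparisons.** Holm compares the smallest p value with 0.05/3, the next with 0.05/2 = 0.025 and the largest with 0.05, stopping at the first failure. Simulated power with a shared control, t tests and n = 23:

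| Assumed effect | Per comparison, fixed → Holm | All three, fixed → Holm |
|---|---|---|
| 15.56 points, SD 20/10, all three modes work | 0.80 → 0.85 | 0.69 → 0.81 |
| d = 1.0, all three modes work | 0.81 → 0.88 | 0.63 → 0.79 |
| 15.56 points, SD 20/10, only one mode works | about 0.80 → 0.80 | not applicable |

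**Why six confirmatory pairs are not a free alternative.** At 0.0083, the two assumed effects give power of 0.71-0.73 with 23 per group and 0.76-0.78 with 25. Reaching 80% takes 27 evaluable patients per group, 108 in all. No 3D-versus-3D difference was ever sized.

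**The case against.** A reader might infer that error control fails in this trial. The document does not support that. The objective, the split of the sizing assumption into control and 3D groups, and the level itself all fit three comparisons with control, and those stay within 5%. Nowhere does the article commit to six confirmatory tests; the 8% belongs to an analysis it does not state, and mainly to the case where all four groups are equal. The trial is labelled exploratory, so a ranking could be answered descriptively. The sentence on a preferable mode concerns usability, not the endpoint for which the level was set, and the independent t test is tied to secondary and descriptive variables. All of this stands.

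A reader might also infer that the plan makes an error by giving power away. It does not. Bonferroni, if that is what was used, is valid, and its cost is already in the sample size for each comparison. The Holm gain is an efficiency gain, largest when all three modes work. Against Dunnett's test, the fixed level loses only about 1 point (0.80 against 0.81).

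It can be said, finally, that naming the family is commonly left to the analysis plan. That is fair as to detail. But the article itself fixes a numerical level and states, for the primary outcome, an aim that the level does not cover. The exploratory label does not resolve this, because the article also promises a global 5% without saying which claims it protects.

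**Conclusion.** The point holds in a limited form. The 0.017 level controls the global 5% for the three 3D-versus-control comparisons and only for those. The aim of finding the most accurate mode in {6b} needs three further pairs with no share of the 5%. Testing all six at 0.017 would give a family-wise error of about 8% under equality of all four groups, against about 4 to 4.5% for the three control comparisons.

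Holm would improve on a fixed 0.05/3 at the same 5%: about 80% to 85-88% per comparison, and about 63-69% to 79-81% for all three, if all three modes work. These power figures rest on effects back-solved from n = 23, on normal data and on t tests, whereas the primary test is Wilcoxon. That Holm never does worse than a fixed 0.05/3 depends on none of these assumptions. That the level came from Bonferroni is inferred from the arithmetic.

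**What to change.** State in Statistical methods {20a} that the primary family consists of the three comparisons of a 3D mode with the CT control, tested with Holm's procedure at a two-sided global 5%. State that 3D-versus-3D differences are reported with confidence intervals, are exploratory and support no confirmatory claim. Reword the aim in {6b}, and the matching expectation in {6a}, so that any statement about the most accurate mode is limited in the same way. A confirmatory Holm procedure over all six pairs should not be offered as an alternative, because the trial was not sized for it.

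The cost is two sentences in {20a} and a small rewording elsewhere. No extra patients, data or visits are needed.
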